## Abstract

**Purpose:**

Microwave ablation (MWA) is a treatment modality for colorectal liver metastases (CRLM). While potentially curative, more information is needed on factors that contribute to long-term local tumour control. The prospective multicentre observational study CIRSE Emprint Microwave Ablation Registry aims to prospectively collect real-world technical data and clinical outcomes on patients treated with MWA in CRLM.

**Methods:**

Eligible patients are adults with up to 9 local treatment naïve CRLM of ≤ 3 cm completely treatable with either MWA alone or MWA with resection and/or radiotherapy within 8 weeks. Data are collected, at baseline, every 3 months until 12 months, and thereafter every 6 months until the end of the study. The primary outcome measure is local tumour control. Secondary outcome measures are overall survival, (hepatic-) disease-free survival, time-to-progression untreatable by ablation, systemic therapy vacation, safety, and quality of life. Covariates related to the primary outcome measure will be assessed using a stratified log-rank test and an univariable Cox proportional hazard regression. A sample size of 500 patients with 750 lesions produces a two-sided 95% confidence interval with a precision equal to 0.057.

**Results:**

Between September 2019 and December 2022, 500 patients have been enrolled with at least 976 treated tumours.

**Conclusion:**

The prospective observational CIEMAR study will provide valuable insights into the real-world use of MWA, helping in the future patient selection and clarifying factors that may contribute to long-term local tumour control.

*Trial Registration*: NCT03775980.

**Graphical Abstract:**

[figure not shown]

**Supplementary Information:**

The online version contains supplementary material available at 10.1007/s00270-023-03573-0.

## Introduction

Thermal ablation is a potentially curative treatment option for patients with colorectal liver metastases (CRLM) [1, 2]. In oligometastatic disease, characterised by one to five metastatic lesions in up to two metastatic sites that can be treated safely by local treatment, surgery remains the standard procedure, achieving a 5-year disease-free survival rate of approximately 20% [3, 4] and a median 5-year survival of 38% [5]. Long-term survival or cure is achievable in 20–45% of the patients who undergo complete A0 thermal ablation [6, 7].

In unresectable and more advanced disease, thermal ablation may be part of a multimodal approach in combination with systemic treatment. Common systemic therapies in early lines are a combination of irinotecan and/or oxaliplatin with 5-fluorouracil/leucovorin together with biologicals such as cetuximab or panitumumab (anti-epidermal growth factor receptor) and bevacizumab or aflibercept (anti-vascular endothelial growth factor) [2]. The randomised phase 2 CLOCC trial has shown that the addition of radiofrequency ablation (RFA)—with or without resection—to systemic treatment prolongs overall survival (OS) significantly (hazard ratio [HR] 0.58, 95% confidence interval [CI] 0.38–0.88, *p* = 0.01) in patients with primarily unresectable CRLM compared with systemic treatments alone [8].

Despite the stronger evidence base for RFA, microwave ablation (MWA) has shown similar effectiveness outcomes [6, 9–12] while adding the benefit of being less susceptible to the heat-sinking effect, which leads to more predictable and larger ablation zones compared with RFA [13–15]. Unlike RFA, MWA is a newer technique and clinical studies on MWA lack systematically collected prospective long-term follow-up data, which limits the understanding of the potential long-term benefits of this ablation modality [16]. The currently ongoing randomised studies COLLISION (NCT03088150), COLLISION-XL (NCT04081168) and NEW-COMET (NCT05129787) also aim to improve these shortcomings [17].

Awaiting the results of these trials, the Cardiovascular and Interventional Radiological Society of Europe (CIRSE) initiated the multicentre prospective observational study CIRSE Emprint™ Microwave Ablation Registry (CIEMAR, NCT03775980). CIEMAR aims to study the long-term effectiveness of MWA in CRLM in the real-world clinical setting, including important parameters such as health-related quality of life (HRQOL), which provides a “real-world” counterpart to the COLLISION trial, to form a substantial evidence base for the use of MWA in CRLM. The study is sponsored and conducted by CIRSE.

## Methods

### Study design

CIEMAR is a prospective, single-arm, multi-centre observational study observing the use of MWA in Europe as performed in routine clinical practice for the treatment of patients suffering from colorectal liver metastases.

The study is governed by a multidisciplinary scientific steering committee including interventional radiologists and liver surgeons. This study was performed in accordance with the declaration of Helsinki and good clinical practice guidelines and was approved by the local ethics committees of participating centres. All patients were required to sign an informed consent for upon study enrolment.

### Site selection and patient enrolment

Sites using Emprint™ or Emprint HP™ as the standard of care for CRLM and meeting a minimum amount of experience (a minimum of 20 ablations of liver tumours using any thermal ablation method per year within the last 4 years) were identified and invited to participate in the study. Centres from 16 European nations (Belgium, Croatia, Denmark, France, Germany, Greece, Italy, the Netherlands, Northern Macedonia, Norway, Portugal, Spain, Sweden, Switzerland, Turkey, and the United Kingdom) were asked to participate.

Patient inclusion and exclusion criteria are displayed in Table 1. Site enrolment started in October 2018 and ended in November 2022. Patient enrolment started in September 2019 and was completed in January 2023.

**Table 1 Tab1:** Patient inclusion and exclusion criteria

Inclusion criteria
18 years old or older
Proven colorectal liver metastases (either histologically or diagnosed by imaging in a patient with known colorectal cancer)
Patient referred to MWA by a multidisciplinary tumour board
Treated with the Emprint or Emprint HP Microwave ablation system
Intention to completely treat (ablation, resection, Stereotactic body radiation therapy [SBRT]) all visible disease within 8 weeks
Max. number of 9 liver lesions
All liver lesions local treatment-naive
Max. diameter of the largest liver lesion treated does not exceed 3 cm

Exclusion criteria
Life expectancy less than 6 months (palliative treatment)
Extrahepatic metastases with the exception of a maximum of 5 lung nodules
Ongoing infection (viral/bacterial)
Patients receiving simultaneous bowel surgery and microwave ablation
Patients receiving simultaneous irreversible electroporation, RFA, SBRT, Cryoablation, high-intensity focused ultrasound, or other local treatment than resection
Pregnancy
Patients with liver metastases that cannot be completely and safely treated
Active cancers other than non-resected primary colon cancer
Advanced liver disease or evidence of liver insufficiency

### Data collection and quality control

Patients enter the study by accepting participation and signing the informed consent form. Baseline data are collected one month prior to the first treatment (see Fig. 1). Additionally, the relevant data to calculate the baseline Charlson Comorbidity Index (CCI) and the clinical risk score (Fong Score) are collected [18, 19]. After each treatment, technical parameters are collected on how the treatment is performed, whether simultaneous resection of other lesions is performed, and whether concomitant systemic therapy is received. Follow-up data are collected 1 month after the treatment, then every 3 months for the first 12 months and then every 6 months until the study exit or study end, 36 months after the 500th patient has been included. Data for safety and adverse events are collected throughout the whole study. HRQOL data are collected before the first treatment and at the first follow-up.

**Fig. 1 Fig1:**
[figure not shown]
Flowchart detailing the data collected at each stage of the enrolment. ECOG: Eastern Cooperative Oncology Group; CCI: Charlson Comorbidity Index

Data validity, completeness, consistency, and uniformity are warranted by case report forms with programmed constraints on data types, ranges, and mandatory data fields. Furthermore, a regular remote monitoring scheme is employed to verify the data quality, inclusion of patients, and follow-ups. No on-site monitoring or source data verification is performed due to resource limitations. Remote monitoring is performed quarterly. Activities include monitoring calls with the sites, sending query reports and monitoring call reports in which all necessary action points are documented. Data are monitored regularly, and queries are raised via the electronic data capturing system. The non-interventional nature of the study means that the exact dates of the procedures and follow-ups are determined by the medical team.

The electronic data collection system was developed and supported by OpenClinica (LLC, Waltham, MA, USA).

### Data sets

For the main results analysis, a full analysis data set composed of all eligible patients who were enrolled in the registry and underwent MWA treatment will be used. Patients for whom the amount of data collected is too scarce to warrant meaningful analysis might be assessed for exclusion. The cut-offs for data scarcity will be evaluated during the final analysis, and the number of excluded patients as well as the reason for exclusion will be reported. Other data sets (e.g. to explore country or centre effects) might be created during the final analysis.

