### Primary outcome measure

The primary outcome measure is the local control rate for all ablated tumours at 1 year (defined as fully ablated with no evidence of disease within the ablation zone at 12 months + / − 45 days after the last ablation of the respective tumour) as assessed by the investigatorsʼ routine protocols (Table 2).

**Table 2 Tab2:** Primary and secondary outcome measures

	Outcome measure	Measured according to	Definition
*Primary outcome measure*			
Effectiveness	Local tumour control at 12 months on a per lesion basis	Investigator assessment	Tumour is considered to be fully ablated with no evidence of disease within the ablation zone at 12 months + / − 45 days after the last ablation
*Secondary outcome measures*			
Safety	Adverse events	CTCAE V5.0	
Effectiveness	Overall survival	Investigator assessment	Time between the first treatment and the time of death of any cause
	Overall disease-free survival	Investigator assessment	Time between the first treatment and the time of any progression, new tumours, or death
	Hepatic disease-free survival	Investigator assessment	Time between the first treatment and the time of any progression of hepatic tumours, new hepatic tumours or death
	Time to untreatable progression by thermal ablation	Investigator assessment	Time between the first treatment and the time of progression of a treated tumour that has been determined as not treatable by thermal ablation
	Systemic cancer therapy vacation	Investigator assessment	Time between the first treatment and the start of systemic cancer therapy
	Quality of Life	EORTC QLQ-C30	

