#### Missing data

Missing observations will be presented as a percentage of the total. For the assessment of the primary outcome measure, a drop-out is defined as a lesion not followed up to the 12 months + / − 45 days mark. In the case of the death of a patient before the 12 months assessment, only lesions that had progressed will be regarded as not having achieved tumour control at 12 months and lesions where progression could not be determined before the death of the patient will be regarded as a drop-out. A sensitivity analysis will be done to assess potential bias due to drop-outs before the 1-year assessment. Depending on the differences between the primary analysis and the sensitivity analysis, a tipping-point analysis may be performed.

The statistical analysis will be done using R Studio version 4.4.

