### Limitations

The limitation of this study is that it has a single-arm observational design without a comparison group. Potentially unaccounted confounding factors may limit the interpretation of the data. Furthermore, as a single-device study using only the Emprint™ Microwave Ablation System and the new generation Emprint™ HP Microwave Ablation Systems, the outcomes may be limited in their generalisability to the numerous MWA devices existing on the market.

The observational design limits the ability to prescribe precise follow-up periods. While a 1-month follow-up after ablative treatment and a 3-month follow-up thereafter can be considered a standard of practice, missing data regarding quality-of-life questionnaires at this time interval can be expected. This will be mitigated with remote monitoring practices but needs to be considered when interpreting the outcomes. Additionally, the lack of on-site monitoring represents a limitation of the study. The data are provided and verified by the sites, but no source document verification is performed.

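### Patients may be dropped from the full analysis set for scarce data at a cut-off chosen during the final analysis, which can remove early deaths and early failures

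*Protocol article*

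**What the plan says.** Under Data sets, the main results are to come from "a full analysis data set composed of all eligible patients who were enrolled in the registry and underwent MWA treatment". The next sentence qualifies this: "Patients for whom the amount of data collected is too scarce to warrant meaningful analysis might be assessed for exclusion". On timing, the article says: "The cut-offs for data scarcity will be evaluated during the final analysis". The safeguard given is that "the number of excluded patients as well as the reason for exclusion will be reported". The article states no threshold, no blinding to outcome when the threshold is set, and no parallel analysis that keeps the excluded patients.

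Other sections already deal with short follow-up. Under Time-to-event, patients lost to follow-up are censored at the last recorded contact, and death is an event for overall survival (OS), disease-free survival (DFS) and hepatic disease-free survival (HDFS). Under Missing data, for the primary outcome, "a drop-out is defined as a lesion not followed up to the 12 months + / − 45 days mark". If a patient dies before the 12-month assessment, lesions that had progressed count as failures and undetermined lesions count as drop-outs. A sensitivity analysis for drop-outs is planned, and a tipping-point analysis is possible.

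**The concern.** An analysis set should be fixed without knowledge of the outcomes it will be used to estimate. Here the membership rule is left open until the final analysis.

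The rule is also tied to a quantity related to outcome. Under Data collection and quality control, visits fall at 1 month, then every 3 months to month 12, then every 6 months. A patient followed to month 36 can contribute about 1 + 4 + 4 = 9 follow-up visits, whereas one who dies in month 2 has about one. A threshold on the amount of data can therefore pick out the second patient, although that patient's record is complete for OS, DFS and HDFS and for a grade 5 adverse event.

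The design makes this matter more. The Limitations section notes that "it has a single-arm observational design without a comparison group", so the absolute estimates are the result and a selection shift cannot cancel between arms.

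**Working it through.** **1. The plan's own figure.** The article gives a precision of 0.057 for 500 patients with 1.5 tumours each (750 lesions) at a control rate of 0.8, by the Wilson method. Full width = 2z·√(p(1−p)/n + z²/(4n²)) / (1 + z²/n), with z = 1.96:
- n = 750, p = 0.8: interval 0.7699 to 0.8271, width 0.0572. The stated 0.057 is reproduced, as a full width.
- n = 976 (lesions treated, from Current status of the study), p = 0.8: width 0.0501, half-width about 0.025.

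Both treat lesions as independent. The half-width of 2.5 points is a yardstick for what follows.

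**2. Removing patients who died.** The documents do not give the number of early deaths or the share a cut-off would remove. Assume 500 patients, 50 deaths within 12 months, and complete 12-month follow-up otherwise. Survival after removing k of the deaths is 450/(500 − k):

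| Deaths removed (assumed) | 12-month survival |
|---|---|
| 0 | 450/500 = 90.0% |
| 5 | 450/495 = 90.9% |
| 10 | 450/490 = 91.8% |
| 25 | 450/475 = 94.7% |

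**3. Removing event-free losses.** The Kaplan–Meier estimate is a product of terms (1 − d/n). Removing a censored patient reduces n at every event time before the censoring time, so each such term falls. If censoring precedes all events, nothing changes. With the same assumed numbers, removing 25 event-free patients lost after the last of the 50 deaths moves 450/500 = 90.0% to 425/475 = 89.5%. If the 25 are lost before the first death, the estimate is 425/475 = 89.5% with or without them. Removal is therefore neutral or unfavourable.

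**4. Safety percentages.** The article reports the percentage of patients with at least one adverse event. If 200 of 500 have one (assumed) and 25 patients with none recorded are removed, 200/500 = 40.0% becomes 200/475 = 42.1%, again unfavourable. Removing patients with a grade 5 event works the other way.

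**5. Primary outcome.** If drop-outs are left out of the denominator, removing a lesion with no determined outcome changes nothing. A shift requires that excluded patients have lesions with determined outcomes, for example documented early progression. For that case only, with an overall rate of 0.80, a share f of lesions removed and control rate e among them, the retained rate is (0.80 − f·e)/(1 − f). Values of f and e are assumed:

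| f | e = 0.6 | e = 0.4 | e = 0 |
|---|---|---|---|
| 2% | 0.804 | 0.808 | 0.816 |
| 5% | 0.811 | 0.821 | 0.842 |
| 10% | 0.822 | 0.844 | 0.889 |

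For example, (0.80 − 0.05 × 0.4)/0.95 = 0.821, a shift of 2.1 points. If e = 0.8 the shift is zero, and at 976 lesions the width rises only from 0.0501 to 0.0515 (5% removed) or 0.0529 (10% removed).

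**6. Order of the rules.** Exclusion under Data sets comes before the censoring and drop-out rules. Once a patient is removed, those rules no longer apply. If the drop-out sensitivity analysis is run on the same set, that patient's lesions are missing from it too.

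**The case against.** The exclusion is conditional: patients might be assessed, and none has to be removed. Numbers and reasons will be reported, and no confirmatory test is planned, so no error rate or success decision depends on the set. Patients with a life expectancy under 6 months are not eligible, and a patient who dies later in the first year would normally have several visits on record. Scarcity could also mean poorly completed forms at a site, in a registry monitored only remotely and without source data verification. Censoring and drop-out rules do not repair missing baseline or procedure fields.

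All of this stands, and it limits the point. A reader might infer that the plan intends to exclude early deaths, or that survival, safety and local control would all be shifted favourably. The documents support neither reading. They do not say who the data-scarce patients are, and steps 3 to 5 show that removing event-free losses, patients without recorded adverse events, or undetermined lesions gives no favourable shift.

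What the objection does not answer is the timing. A separate statistical analysis plan could have fixed a cut-off in advance, but the article itself assigns that choice to the final analysis. A count of exclusions with reasons tells the reader that patients were removed, not what the estimates would have been with them.

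**Conclusion.** The concern holds in a limited form. The article allows the main analysis set to be altered for scarce data by a threshold set when outcomes are known, and data volume depends on time alive and in follow-up. The clearest exposure is for OS, DFS, HDFS and grade 5 events, where an early death is a complete observation. For local control the exposure is narrower: loss of documented early failures, and a weaker drop-out sensitivity analysis if that uses the same set.

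The article supports no figure for the bias and no single direction. The move from 90.0% to 94.7% rests on assuming 50 deaths within 12 months with half of them removed, and smaller removals give smaller shifts. The local-control shifts of 0.4 to 8.9 points rest on 2% to 10% of lesions being removed, all with determined outcomes and with control rates between 0.6 and 0. This should be fixed. Because the exclusion is optional and the study is descriptive, it falls short of a defect that must block the analysis.

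**What to change.** Delete the data-scarcity exclusion from the main analysis. Keep every eligible patient with at least one MWA in the full analysis set, and let the censoring rule under Time-to-event and the drop-out rule under Missing data handle short follow-up.

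If an evaluable subset is wanted, define it before data lock on baseline and procedure fields only (for example, no recorded MWA date). Use it only as a sensitivity analysis, and report results with and without the exclusions.

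The cost is about one sentence in the analysis plan before data lock, with no further data collection. Estimates may turn out slightly less favourable than under a selective exclusion.

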### Primary outcome measure

The primary outcome measure is the local control rate for all ablated tumours at 1 year (defined as fully ablated with no evidence of disease within the ablation zone at 12 months + / − 45 days after the last ablation of the respective tumour) as assessed by the investigatorsʼ routine protocols (Table 2).

**Table 2 Tab2:** Primary and secondary outcome measures

	Outcome measure	Measured according to	Definition
*Primary outcome measure*			
Effectiveness	Local tumour control at 12 months on a per lesion basis	Investigator assessment	Tumour is considered to be fully ablated with no evidence of disease within the ablation zone at 12 months + / − 45 days after the last ablation
*Secondary outcome measures*			
Safety	Adverse events	CTCAE V5.0	
Effectiveness	Overall survival	Investigator assessment	Time between the first treatment and the time of death of any cause
	Overall disease-free survival	Investigator assessment	Time between the first treatment and the time of any progression, new tumours, or death
	Hepatic disease-free survival	Investigator assessment	Time between the first treatment and the time of any progression of hepatic tumours, new hepatic tumours or death
	Time to untreatable progression by thermal ablation	Investigator assessment	Time between the first treatment and the time of progression of a treated tumour that has been determined as not treatable by thermal ablation
	Systemic cancer therapy vacation	Investigator assessment	Time between the first treatment and the start of systemic cancer therapy
	Quality of Life	EORTC QLQ-C30	

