#### Time-to-event

The first MWA treatment will be the starting point for the per-patient time-to-event analyses, and the first MWA treatment of the respective lesion for per-lesion time-to-event analyses. OS is defined as the time of death of any cause, for DFS as the time of any progression, new tumours, or death, for HDFS as the time of any progression of liver tumours, new tumours in the liver or death and for time to progression untreatable by thermal ablation as the time of progression of a treated tumour that has been determined as not treatable by thermal ablation according to the investigator. Systemic cancer therapy vacation is defined as the time between the first MWA treatment and the start of systemic cancer therapy. In these analyses, subjects lost to follow-up will be censored at the last recorded communication with the patient.

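### Primary local control is dated from each lesion's last ablation, so it is control allowing re-ablation, while the per-lesion covariate analysis is dated from the first ablation

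*Protocol article*

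**What the plan says.** **Primary outcome.** The section Primary outcome measure and Table 2 define the outcome as "Local tumour control at 12 months on a per lesion basis". A lesion succeeds if it is fully ablated with no disease in the ablation zone at 12 months ± 45 "days after the last ablation of the respective tumour". Table 1 requires an intention to treat all visible disease within 8 weeks, but nothing ties the last ablation to that period.

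**Per-lesion time-to-event analyses.** The section Time-to-event sets the origin at "the first MWA treatment of the respective lesion for per-lesion time-to-event analyses". It does not say which event ends the per-lesion time.

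**Link between the two.** The abstract (Methods) states: "Covariates related to the primary outcome measure will be assessed using a stratified log-rank test and an univariable Cox proportional hazard regression". The Discussion adds that 1-year control per lesion will be used to find factors affecting the effectiveness of MWA.

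**Death before assessment.** The section Missing data says "only lesions that had progressed will be regarded as not having achieved tumour control at 12 months". It makes no exception for a lesion that progressed and was then re-ablated.

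**The concern.** The time origin of the primary outcome can be moved by the outcome itself. A local recurrence prompts a further ablation, that ablation becomes the last one, and the 12-month assessment moves with it. A reader who sees a 1-year local control rate after MWA may take it as the rate at which the initial ablation holds. On the literal definition it also includes lesions that failed once and were rescued.

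Two consequences follow. The covariate analysis is counted from the first ablation, so it may explain a different quantity from the one reported. And the death rule treats earlier progression as final, whereas the definition for survivors lets re-ablation undo it.

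**Working it through.** **1. The same lesion under each rule.** Take a lesion that recurs locally at month 10 after its first ablation and is re-ablated that month.

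- *Primary outcome:* assessment moves to month 10 + 12 = 22. If the zone is clear then, within ± 45 days, the lesion is a success.
- *Per-lesion time-to-event:* the clock started at the first ablation. If the event is local progression, the lesion has an event at month 10. The article does not define this event; local progression is the natural reading because local control is the only outcome defined per lesion.
- *Patient dies before the assessment:* the lesion had progressed, so it is a failure under Missing data, despite the re-ablation.

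The per-patient endpoints also differ. Disease-free survival counts the recurrence, since its definition is "Time between the first treatment and the time of any progression, new tumours, or death". Time to untreatable progression does not, because it needs the "time of progression of a treated tumour that has been determined as not treatable by thermal ablation according to the investigator".

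**2. The plan's own precision figure, as a yardstick.** Inputs from Sample size calculation: 500 patients × 1.5 tumours = 750 lesions, proportion 0.8, two-sided 95% Wilson interval (z = 1.96).

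- Centre = (p + z²/2n) / (1 + z²/n) = (0.8 + 0.00256) / 1.00512 = 0.7985
- Half-width = z·√[p(1−p)/n + z²/4n²] / (1 + z²/n) = 0.0286
- Interval 0.7699 to 0.8271; full width 0.0572

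The stated 0.057 reproduces, as a full width.

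**3. Illustrative size.** The documents give no rates for local recurrence, re-ablation or success of re-ablation, so all three are assumptions. Let f be the share of lesions with local progression within 12 months of the first ablation, q the share of these re-ablated, and s the share of re-ablated lesions clear 12 months later.

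- Control from the first ablation = 1 − f
- Control from the last ablation = 1 − f + f·q·s

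With f = 0.20, q = 0.3 to 0.7 and s = 0.7 to 0.8:

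- Low: 0.80 + 0.20 × 0.3 × 0.7 = 0.842
- High: 0.80 + 0.20 × 0.7 × 0.8 = 0.912

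The gap is 0.042 to 0.112, or 0.042/0.0572 = 0.7 to 0.112/0.0572 = 2.0 times the planned full width.

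With wider ranges (q = 0.25 to 0.75, s = 0.6 to 0.8):

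| f | From first ablation | From last ablation |
|---|---|---|
| 0.20 | 0.80 | 0.83 to 0.92 |
| 0.30 | 0.70 | 0.745 to 0.88 |
| 0.40 | 0.60 | 0.66 to 0.84 |

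The formula leaves out drop-outs and recurrences after month 12. A late recurrence can work the other way: a lesion clear at month 12 but re-ablated at month 20 is assessed at month 32, and could then become a failure.

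**The case against.** **Control allowing repeat ablation is a legitimate quantity.** The origin is stated openly in both text and table, and the outcome concerns ablated tumours, not the durability of a single session. This stands: the definition is not an error in itself, and calling the rate biased presumes a target that the article does not set. What is missing is a label and a limit on what counts as the last ablation. The requirement that the tumour be fully ablated could mean that the last ablation is the session completing the initial treatment, but the article does not say so.

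**The contradiction in events is inferred.** A reader might conclude that the plan expressly counts a re-ablated recurrence as a success in one analysis and an event in the other. The documents do not go that far, because the per-lesion event is undefined and may be fixed in the full protocol or SAP. The difference in origin is explicit; the difference in event is the natural reading only.

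**The visit schedule.** A reader might also infer that re-ablated lesions are selectively lost, because follow-up runs "then every 3 months for the first 12 months and then every 6 months until the study exit or study end" and a shifted 12-month mark could fall between visits. That needs visits counted from the first treatment and held on exact days. The article does not state that origin, and it leaves dates to the medical team. A share of lesions lost this way cannot be supported.

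**The study is not confirmatory.** No hypothesis is tested in a confirmatory sense, and the explicit link between covariate tests and the primary outcome is one sentence in the abstract. Both are true, but the Discussion makes the same link in general terms, and the rate with its covariates is the main product of the study.

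**Conclusion.** The point holds as a matter of definition. The primary rate, read literally, is 12-month control allowing re-ablation, and the per-lesion analysis meant to explain it starts at a different time. The death rule fits poorly with a clock that re-ablation can restart.

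The size is unknown. The 4 to 11 points at 20% recurrence show only that the choice of origin could matter as much as the planned precision. They rest wholly on assumed rates and on equating first-ablation control with 80%, whereas the article's 60%, 70% and 80% planning scenarios are not tied to either origin.

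A reader might infer that the primary outcome must be replaced. The documents do not support that: the published definition is a valid estimand, and enrolment is complete. A second figure and a matched covariate analysis are enough.

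**What to change.** 1. Keep the published figure, but name it as local control allowing re-ablation (assisted control).
2. Report beside it 12-month local control from the first ablation of each lesion, or from the end of the initially planned course within the 8-week period. Any later local progression is a failure, even if re-ablated. State how re-ablation of residual disease within the initial course counts, as distinct from re-ablation of a later recurrence.
3. Define the per-lesion event, and use the origin and event from item 2 in the per-lesion Kaplan–Meier, log-rank and Cox analyses.
4. For each figure, apply one rule to re-ablated lesions whether or not the patient dies before the 12-month assessment. The present death rule already fits the figure in item 2; it needs reconciling with the assisted figure.

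The cost is one extra analysis and a second figure likely to be somewhat lower than the first. It needs ablation dates per lesion. The article says that technical data are collected after each treatment but does not state that these dates are held per lesion, so this should be confirmed. Final results are expected by 2027, so the definitions should be settled before the final analysis.
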